### Data collection, management, and analysis

*Data collection methods:* The interviews, evaluation of radiological images, application of instruments and measurements of pain, edema, and flexibility will be carried out only by a single qualified, trained physiotherapist, with familiarity with the instruments and with adequate training. Blood sample collection will be performed by a nursing professional familiar with this procedure. Laboratory analyzes will be performed by another researcher qualified biomedical pharmacist. The application of the intervention protocols will be carried out by two physiotherapists trained in aquatic physiotherapy and who will not participate in the interviews, radiological analysis and evaluation of edema, pain and flexibility.

*Data management:* All data will be entered electronically
*via* Microsoft Excel. The study’s digital forms will be inserted and received in a cloud file with access only to the researcher. Participant files will be stored in numerical order and stored in storage for a period of 3 years after completion of the study. Modifications to data recorded in the database will be documented through the data breach system associated with your user identification code and password. Access to study data will be restricted. All reports will be prepared in such a way that no subject can be identified.

### Statistical analysis

The resulting data will be tabulated, considering the absolute values and their respective standards. Information regarding the main outcome corresponding to the variations in the concentrations of MMP-3 and GPx in peripheral blood due to three different aquatic physiotherapy interventions will be comparatively evaluated among the distinct interventions and among the different times (in pre- and post-intervention moments).

The information on the outcome regarding pain, edema, and flexibility will be comparatively assessed among the different types of intervention. Statistical analyses will be performed in the SPSS software and will be considered as a significance level when p>0.05 through the repeated measures ANOVA statistical test.

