**Methods:**

This will be a crossover randomized controlled trial in which 15 individuals will be submitted to three aquatic physiotherapy modalities with a minimum 15-day wash-out period in patients over 50 years old and diagnosed with OA in at least one knee, presence of pain and at least one functional dysfunction for at least 6 months, absence of physical limitation that prevents the exercise protocol from being performed, Kellgren and Lawrence ranking between I and IV, walk independently and without auxiliary device. Variations in the concentrations of MMP-3 and GPx in peripheral blood, pain, edema, and flexibility resulting from the three aquatic physiotherapeutic interventions will be evaluated both pre- and immediate post-intervention. The reference group will be submitted to the same aquatic physiotherapy protocols, however, only the biochemical parameters and the self-perception questionnaires will be evaluated.

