## Methods

### Trial design

This is an interventional transversal study, randomized clinical trial, crossover type with three arms: low, medium, and high-intensity aquatic physiotherapy.

This clinical intervention protocol follows the recommendation from the Standard Protocol Items: Recommendations for Interventional Trials (SPIRIT).
^
31
^
^,^
^
32
^ The study sample, defined according to criteria, will be submitted to a single session of each one of the following modalities of aquatic physiotherapy: (a) low-intensity, (b) medium-intensity, and (c) high-intensity. Among each modality, a minimum of a 15-day wash-out period will be respected, in accordance with
Figure 1.

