**Figure 1. f1:**
[figure not shown]
Flow of interventions and assessment parameters.

For this study, 15 participants will be recruited. The sample size calculation indicated a non-centrality parameter (δ) of 3.8, suggesting a moderate effect on biomarker variations. The critical t-value was 2.10, with degrees of freedom (df) of 16.143, resulting in a total sample size of 15 participants and an actual power of 0.95. The effect size calculation was based on means and standard deviations, and for our main dependent variables, these were reported by previous investigations: Germanou
^
33
^ through the antioxidant levels and Nascimento
^
34
^ through the MMP-2 and MMP-9 analysis between the control and intervention group, in this case, it is represented by patients with knee osteoarthritis.

The assessment parameters used in each variable will consist of instruments that allow for the assessment of the variations in the MMP-3 concentration, oxidative stress, pain, edema, and flexibility. In addition, a self-perception questionnaire, developed by the authors, will be applied to assess self-perception. It consists of a Likert scale where the patient must classify their perception of well-being between zero and 10, where zero represents the worst feeling of well-being and 10 represents the best feeling of well-being. The data collection form, informed consent form and patient identification form can be found as
*Extended data.*
^
32
^ The trial has been registered on
ClinicalTrials.gov (
NCT05610696, 18/01/2023).

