### Outcomes

Initially, all participants will be interviewed and evaluated in relation to the degree of osteoarthritis and functionality. Information regarding the patient data will be confirmed
*via* interview, considering data such as complete name, date of birth, age, affected knee(s), duration of pain, arterial blood pressure, list of medications in use, consumption of tobacco or alcohol, associated diseases, if they are undergoing physiotherapy treatment or regular physical activity.

The classification regarding the degree of osteoarthritis will be performed by analyzing the radiograph of the affected knee according to the method of Kellgren and Lawrence. The radiographs will be analyzed, the degree of osteoarthritis will be identified with the negatoscope support, and the images in the digital form will be displayed on a computer screen, considering the classification expressed in degrees ranging from zero to IV.

Subsequently, the identification of functionality will be assessed according to the Brazilian version of the Knee Injury and Osteoarthritis Outcome Score (KOOS). The KOOS questionnaire was developed in the 1990s as an instrument to evaluate the patient’s perception of their knee and associated problems. Since its first publication in 1998, the psychometric properties of KOOS were evaluated in a systemic review of 37 articles demonstrating adequate validity in its use for the study population.
^
37
^

Regarding the pre- and post-intervention assessment instruments, all participants will have the following parameters evaluated: concentration of MMP-3 and GPx, pain, edema, flexibility, and self-perception of the general well-being. In addition, it should be noted that in the 24-hour-follow-up, only the biochemical concentrations and the self-perception questionnaire will be reevaluated.

The biochemical variables will be measured in peripheral blood from the concentrations of MMP-3 and GPx. The levels of MMPs will be measured based on the Enzyme-Linked Immunosorbent Assay (ELISA) methodology, which is based on the antigen-antibody interaction and will be performed according to the kit manufacturer’s instructions. MMP-3, a constituent of the stromelysin family that is an important mediator responsible for the degradation of collagen type II, IX, and XI,
^
12
^
^,^
^
13

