^ will be considered for this analysis. Oxidative stress will be measured by analyzing the peripheral blood from percutaneous punction. The sample collection time will be performed according to the study by Nascimento
^
34
^ and will be in accordance with the following times: T0 (immediately before the intervention), T1 (immediately after the intervention), and T2 (24 hours after the intervention).

The assessment of the degree of pain will be performed using the visual analogue pain scale,
^
38
^ from a scale graduated from zero to 10, in which zero corresponds to cases without pain and 10 corresponds to the worst imaginable pain.

The assessment of edema will be performed based on the measurement of the circumference of the affected knee(s). The measure will be performed with the patient relaxed in dorsal decubitus and the circumference will be determined with the knee in extension, based on the proximal distance of 1 cm from the base of the patella.
^
39
^ For that, the same measuring tape will be used for all measurements.

The flexibility will be assessed by measuring the amplitude of the active and passive movement for the knee flexion and, for that, a conventional goniometer will be used. The goniometer will be used because it has a low cost, is easy to handle, allows the assessments to be performed quickly, and the measurements and movement amplitude for the knee joint are valid and reliable.
^
40
^ For the assessment, the knee will be free of clothing, and the patient will be positioned in dorsal decubitus with the hip articulation at 90° of flexion. The fixed arm of the goniometer will be positioned parallel to the thigh with an orientation towards the greater trochanter of the femur and the mobile arm will be parallel to the lateral face of the fibula, directed towards the lateral malleolus. The movement reading will be performed while maintaining the final possible position of the arc of movement where the highest reading degree represents the assessed measurement.
^
41
^ All procedures will be performed by a single physiotherapist.

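### Two unranked main markers and several ANOVA comparisons share one 0.05 level, so the chance of a false main finding is about 8–10%, or 16–19% if the intervention and time tests both count

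*Protocol article*

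**What the plan says.** The Statistical analysis section defines the main outcome in one sentence that opens "Information regarding the main outcome corresponding to the variations in the concentrations of MMP-3 and GPx in peripheral blood". MMP-3 and GPx stand side by side and neither is put first. The sentence goes on to say that this information "will be comparatively evaluated among the distinct interventions and among the different times (in pre- and post-intervention moments". The decision rule is that results "will be considered as a significance level when p>0.05 through the repeated measures ANOVA statistical test". The inequality is printed the wrong way round; I read it as a 0.05 threshold.

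Trial design gives the number of programs: "crossover type with three arms: low, medium, and high-intensity aquatic physiotherapy". Outcomes gives the blood sampling times: "T0 (immediately before the intervention), T1 (immediately after the intervention), and T2 (24 hours after the intervention". It confirms that the last one applies to the markers: "in the 24-hour-follow-up, only the biochemical concentrations and the self-perception questionnaire will be reevaluated". The Methods paragraph of the abstract lists the markers together with pain, edema and flexibility, and says that they "will be evaluated both pre- and immediate post-intervention", with no 24-hour point.

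The sample size paragraph under Trial design reads: "The sample size calculation indicated a non-centrality parameter (δ) of 3.8". It adds a critical t of 2.10, df of 16.143, 15 participants and power of 0.95. It refers to main dependent variables in the plural, and does not say which marker or contrast the calculation powers.

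**The concern.** A main outcome made of two unranked markers offers more than one route to a main finding. A repeated measures ANOVA over programs and times also yields several F tests per marker: intervention, time and their interaction. The article does not say which is decisive.

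These terms answer different questions. The intervention main effect averages over all sampling times, including T0, which precedes the session. The time effect says nothing about intensity. The interaction, or equivalently a comparison of programs on change from T0, bears on whether intensity matters. With two post-session samples, which change counts is also open.

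If any of these may be reported as the main result at 0.05, the overall false-positive rate exceeds 5%. The Discussion says that the results will point the way for future longitudinal studies, so a chance result on one marker could set their direction.

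**Working it through.** **1. The article's own power figure.** Inputs, from the sample size paragraph: noncentrality δ = 3.8, df = 16.143, critical t = 2.10.

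- Two-sided 0.05 at df 16.143 gives critical t = 2.118. Power from the noncentral t is P(|T| > 2.118 | δ = 3.8) = 0.946. With the printed 2.10 it is 0.948.
- One-sided 0.05 gives critical t = 1.745 and power 0.977, which does not fit.

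The stated 0.95 is therefore reproduced as one two-sided comparison at the full 0.05. The article does not print that alpha; it is inferred from the critical t.

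**2. Chance of at least one false finding, independent tests.** Formula: 1 − 0.95^m.

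- m = 2 (one F test per marker): 1 − 0.95² = 9.75%
- m = 4 (intervention and time F per marker): 1 − 0.95⁴ = 18.5%
- m = 6 (all three ANOVA terms per marker): 1 − 0.95⁶ = 26.5%
- m = 12 (2 markers × 3 pairs of programs × 2 post-session times): 1 − 0.95¹² = 46.0%

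**3. Allowing for dependence.** Markers may be correlated, and contrasts share a baseline and sessions. A null simulation used 15 participants, three sessions, three times, two markers and 20,000 runs. Assumptions not in the article: normal data, standard deviations of 1.0 (participant), 0.7 (session) and 1.0 (residual), sphericity, no period or carry-over effect, and between-marker correlation from 0 to 0.8.

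| Tests counted as main | Correlation 0 | Correlation 0.8 |
|---|---|---|
| One F per marker (interaction) | 9.9% | 7.7% |
| Intervention F and time F per marker | 18.7% | 15.8% |
| All three F terms per marker | 26.8% | 22.4% |
| All 12 pairwise change contrasts, unadjusted | 39.1% | 32.5% |

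Simulation error for a rate near 10% is about √(0.10 × 0.90 / 20,000) = 0.2 percentage points. A second simulation of 40,000 null trials, with one 2-df test of intensity per marker (F with 2 and 28 df), gave 9.6% to 7.9%, in line with the first row.

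At a between-marker correlation of practically 1, the first row falls to 4.8% and the second to 9.4%. The nominal 5% is recovered only if the markers are almost interchangeable and a single F test per marker counts.

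**4. Price of control.** At δ = 3.8 and df = 16.143, a test at 0.05 has power 0.946 and a test at 0.05/2 = 0.025 has power 0.895. Under Holm the smaller p-value is tested at 0.025 and, if that succeeds, the other at 0.05. If these δ and df applied to each marker, power per marker would lie between 0.895 and 0.946.

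**The case against.** The article names one method, an omnibus ANOVA, and nowhere lists pairwise tests. A reader might multiply two markers, three pairs and two times into 12 tests and take roughly 32–40% as the error rate of this plan. The text does not support that. The figure is an assumed worst case, and post-hoc adjustment is commonly left to an analysis plan that is not shown here. That part of the objection stands.

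A reader might also conclude that with 15 people a chance positive is likely. It is not: even the assumed worst case stays below one half, and the type I error of a valid test does not rise because the sample is small. Nor does the article state a success rule allowing a claim on any marker at any time; it simply leaves the choice open.

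The study is partly exploratory, concerns a single session and defers to later longitudinal work, which lowers the stakes. The time-point mismatch is thin: Outcomes is explicit about T0, T1 and T2, and the abstract condenses several outcomes into one sentence.

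What the objection does not remove is what the text itself fixes: two equal main markers, compared among programs and among times, at one 0.05 level. An unseen plan could add an adjustment, but the stated power of 0.95 corresponds to an unadjusted test and would then need revising.

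**Conclusion.** The point holds in a limited form. As written, the chance of at least one false main finding is about 8–10% if one F test per marker counts, and about 16–19% if the intervention and time F tests the section describes both count. The second range assumes no true time effect. If a session really shifts a marker, a significant time test for that marker is not a false finding, and the rate falls towards the first range. Both ranges rest on the simulation assumptions given and on between-marker correlation of at most 0.8.

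This does not invalidate the design. It is a decision rule that exceeds its nominal level and can be repaired cheaply before recruitment, since the article gives the study status as not yet recruiting.

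**What to change.** Before recruitment, state in the Statistical analysis section:

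- **One decisive test per marker:** the overall (2-df) intensity effect on change from T0 at one named post-session time. The other time is secondary. Nothing in the article ranks the markers or the times, so the choice is the sponsor's to make and justify.
- **Control across the two markers:** Holm, or a fixed order with the first marker chosen and justified by the sponsor.
- **Pairwise program contrasts** for a marker only after its overall test is significant, at the level at which that test was passed. With exactly three programs this protects the error rate within that marker.

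The abstract should name the same post-session time, and the printed direction of the 0.05 threshold should be corrected in the same edit.

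**Cost.** No extra data or participants are needed for the wording. Under Holm the first test is at 0.025, so power per marker falls from about 0.946 to about 0.895 at worst. Under a fixed order each test keeps 0.05, but the second marker can be claimed only if the first succeeds. The current power calculation is a t-type comparison drawn from control-versus-intervention results, not a 2-df test among three programs, so the power statement must be redone for the chosen test. Whether 15 participants still suffice cannot be judged until then.

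### Pre-session MMP-3 and GPx (T0) are a time level of the repeated measures ANOVA and the tested term is not named; T0 as a covariate would use the same data more efficiently at n = 15

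*Protocol article*

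**What the plan says.** All places are in the protocol article.

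- **Outcomes** sets three blood samples for every session: "T0 (immediately before the intervention), T1 (immediately after the intervention), and T2 (24 hours after the intervention".
- **Statistical analysis** defines the "main outcome corresponding to the variations in the concentrations of MMP-3 and GPx in peripheral blood" and says these values "will be comparatively evaluated among the distinct interventions and among the different times (in pre- and post-intervention moments", "through the repeated measures ANOVA statistical test". No covariate is mentioned. The section does not say whether the programs are compared by the intervention main effect or by the intervention-by-time interaction.
- **Trial design**, in the sample-size paragraph, reports a t-type calculation, "resulting in a total sample size of 15 participants and an actual power of 0.95".

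**The concern.** The trial asks whether three exercise intensities differ in their effect on two blood markers. T0 is drawn before the session, and the order of programs is randomized, so T0 cannot respond to the program about to be given. It does carry information about the values that follow, and the efficient use of that information is to adjust for it. As one of the compared times it serves less well:

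- **Intervention main effect.** T0 is averaged into the outcome, which shrinks the program effect.
- **Intervention-by-time.** T0 is the reference for change. The effect stays whole, but T0 is subtracted with a slope of 1 whatever the correlation, and with three times the test spreads over 4 df.

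With 15 participants, lost precision makes it more likely that a real difference between intensities is missed. The article intends the results to guide later longitudinal studies, so a missed difference would carry forward.

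**Working it through.** **Step 1: the plan's own figure.** The inputs are "The sample size calculation indicated a non-centrality parameter (δ) of 3.8, suggesting a moderate effect on biomarker variations" and "The critical t-value was 2.10, with degrees of freedom (df) of 16.143".

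- Noncentral t with δ = 3.8 and df = 16.143 gives power 0.948 at critical value 2.10, and 0.946 at the exact two-sided 5% value of 2.118. The stated 0.95 reproduces.
- N = 15 does not. Fifteen pairs give 14 df, and two groups totalling 15 give 13. The stated df fits a two-group Wilcoxon-Mann-Whitney calculation with N = 19 (19 × 3/π − 2 = 16.144).
- The calculation is therefore for neither ANOVA term, and the paragraph yields no usable effect size. The anchor below, 3.8/√15 = 0.98 SD, is an assumption.

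**Step 2: one post value.** Let r be the within-session correlation after participant effects are removed (not in the documents), with unit variance at each time. Error variance, scaled to the full program effect on T1:

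- T0 as covariate: 1 − r²
- interaction (the T1 − T0 change): 2(1 − r)
- main effect over T0 and T1: the signal is 1/2 and the variance (1 + r)/2, so the scaled variance is 2(1 + r)

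Relative to the covariate model the ratios are 2/(1 + r) and 2/(1 − r). At r = 0.5 they are 1.33 and 4, so about 20 and 60 participants would be needed for what 15 give. If the effect is set so that the covariate model has 80% power (noncentral F; error df 25 with the covariate, 26 without):

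| r | interaction | main effect |
|---|---|---|
| 0.3 | 61% | 36% |
| 0.5 | 67% | 27% |
| 0.7 | 73% | 17% |
| 0.9 | 78% | 9% |

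**Step 3: three times, effect equal at T1 and T2.** Assumed effects are 0, 0.49 and 0.98 SD for low, medium and high; n = 15; α = 0.05 two-sided; equal correlation r between all times. The signal is 15 × 2 × (0.981/2)² = 7.22, and the noncentrality is 7.22 divided by the error variance.

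- Main effect: signal factor 2/3, variance (1 + 2r)/3
- Change of mean(T1, T2) from T0, 2 df: variance 1.5(1 − r), which is 1.05, 0.75, 0.45 and 0.15 at r = 0.3, 0.5, 0.7 and 0.9
- T0 as covariate for mean(T1, T2): variance (1 + r)/2 − r², which is 0.56, 0.50, 0.36 and 0.14

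Power by simulation, with noncentral F as a cross-check:

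| r | main effect | interaction, 4 df | change score, 2 df | T0 as covariate |
|---|---|---|---|---|
| 0.3 | 54% | 49% | 60% | 86% |
| 0.5 | 44% | 66% | 75% | 89% |
| 0.7 | 38% | 88% | 93% | 97% |
| 0.9 | 33% | about 100% | about 100% | about 100% |

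The last two columns isolate the role of T0. The gain is 86 − 60 = 26, 89 − 75 = 14 and 97 − 93 = 4 points. Repeat runs gave 24 to 26, 12 to 14 and 3 to 4. Without any program effect, every test rejected in about 5% of trials.

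**Step 4: the same effect at T1 only.** At r = 0.3, 0.5 and 0.7:

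- covariate model on pooled T1 and T2: 31%, 34%, 44%
- three-time interaction: 49%, 65%, 88%
- T1 − T0 change, 2 df: 47%, 62%, 84%
- T1 contrast with T0 as covariate: 64%, 73%, 89%

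Pooling loses when the effect does not last to 24 hours. A T1 contrast with T0 as covariate gains 17, 11 and 5 points over its own change score, and 15, 8 and 1 points over the interaction.

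**The case against.** **The planned analysis is valid.** With randomized sequences neither ANOVA term is biased, and type I error is near 5%. This stands: the point is about efficiency.

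**Variations in concentration suggest change.** The main outcome is worded that way, which points to the interaction, where nothing is diluted. The comparison among interventions and among times can equally be read as two main effects. A reader might infer that the plan dilutes the program effect, or that its power is only about 44%. The documents support neither. Shrinkage to two thirds (or to half over T0 and T1) belongs to the main effect alone, and the tested term is not named.

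**The gain can be overstated.** Comparing the covariate model with the better ANOVA term in Step 3 gives differences of 32, 23 and 9 points (86 − 54, 89 − 66, 97 − 88). At correlations 0.5 and 0.7, part of that comes from setting a 4-df test against a 2-df test; at 0.3 the better term is the diluted main effect. The like-for-like gain is smaller, and the ranking reverses for a pooled outcome if the effect is at T1 only. Both objections stand.

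**A short article may leave model detail to the analysis plan.** This holds for contrasts in general. But the text does fix the pre-session moment as a compared time, so T0's role is a stated choice that can be improved, and the recommendation does not rest on missing detail.

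**Conclusion.** The point holds as an efficiency recommendation. T0 is a level of the time factor, the term that answers the trial's question is not named, and either term uses T0 less well than a covariate would.

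The size cannot be fixed from the documents. It rests on three assumptions: the within-session correlation, the 0.98 SD difference, and how long the effect lasts. For an effect equal at T1 and T2, the covariate gains about 24 to 26, 12 to 14 and 3 to 4 points over a 2-df change score at correlations 0.3, 0.5 and 0.7, and almost nothing at 0.9. The loss is much larger if the main effect is the intended test. The stated power of 0.95 cannot be carried over to either term.

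**What to change.** For MMP-3 and GPx, rewrite the analysis paragraph as follows:

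- Take the post-session values as outcome in a within-participant model with program and period as factors.
- Enter that session's T0, centred within participant, as a covariate, and not as an outcome level.
- Name the tested contrast by time point, for example program at T1 as the acute effect, with T2 tested separately. Say which one carries the conclusion.
- Do not pool T1 and T2 into a single program test. If the effect does persist, this gives up some power (at r = 0.5, 73% for T1 alone against 89% pooled), but it protects against the T1-only case (73% against 34%).
- Keep the T0-T1-T2 profile as description.

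The cost is one residual degree of freedom and a slightly different SPSS model. No new data are needed, and the article gives the study status as not yet recruiting. If the ANOVA is kept, the least change is to name intervention-by-time as the test of the program comparison.

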### Assignment of interventions

*Allocation:* Participants will be allocated randomly to establish the sequence within each group, following a computer-generated randomization schedule from
randomize.com, as exemplified by the flowchart in
Figure 1.

*Blinding:* This study is classified as single-blinded, indicating that the researchers responsible for conducting the assessment instruments and laboratory analysis procedures will be distinct from those administering the intervention protocols.

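### The named repeated measures ANOVA has no period term although the trial is a three-period crossover; this costs power for per-session comparisons and when data are incomplete, but causes no average bias

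*Protocol article*

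**What the plan says.** - **Design.** The protocol article's Trial design section describes a "randomized clinical trial, crossover type with three arms: low, medium, and high-intensity aquatic physiotherapy". Between sessions, "a minimum of a 15-day wash-out period will be respected".
- **Allocation.** Under Assignment of interventions: "Participants will be allocated randomly to establish the sequence within each group". The number of orders and their balance are not given in the text. The section refers to Figure 1, which is not shown.
- **Sampling.** Under Outcomes, blood is taken at "T0 (immediately before the intervention), T1 (immediately after the intervention), and T2 (24 hours after the intervention".
- **Analysis.** Under Statistical analysis, MMP-3 and GPx "will be comparatively evaluated among the distinct interventions and among the different times (in pre- and post-intervention moments"; pain, edema and flexibility "will be comparatively assessed among the different types of intervention". The test is given as "through the repeated measures ANOVA statistical test", in SPSS.
- **Not stated.** No section carries period or sequence into the analysis, says how missing values are handled, or gives an allowance for dropout in the 15 participants.

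**The concern.** In a crossover each person's sessions differ in programme and also in calendar position. Three sessions at least 15 days apart span at least 30 days. Symptoms, familiarity with the pool and the exercises, and assay conditions can all shift over that time. The wash-out protects against carry-over; it does nothing about such drift. Randomising the order makes the drift separable from the programme effect, but only a model with a period term uses this. Without one, the drift inflates the residual variance of comparisons made on one value per session.

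The second concern is that classical repeated measures ANOVA in SPSS keeps only participants with every programme-by-time cell filled. With 15 people, one missed session removes that person's other two sessions as well.

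**Working it through.** **The plan's own figure.** Inputs from the Trial design section: noncentrality 3.8, df 16.143, N = 15, power 0.95. The noncentral t distribution (two-sided 5%) gives power 0.946 at df 16.143. Read as a paired comparison with n = 15 (df 14), dz = 3.8/√15 = 0.98 and power is 0.942. The stated power reproduces. The df does not match a paired design with 15 people, but that is a separate matter; dz 0.98 is used below only as the implied target.

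**Period omitted, one value per session.** Assumptions: within-person SD 1; drift 0.5 SD per period; programme effects 0, 0.4 and 0.9 SD; 15 people in period-balanced orders.
- Drift values centred on their mean are −0.5, 0 and 0.5, so the period sum of squares is 15 × (0.25 + 0 + 0.25) = 7.5.
- Without a period term this goes into the residual, which has 2 × 15 − 2 = 28 df. The expected residual mean square rises from 1 to 1 + 7.5/28 = 1.27.
- With a period term the residual has 26 df and no inflation.
- Simulated power over repeated runs: 0.41 to 0.43 without period, 0.53 to 0.56 with it.
- Simulated type I error: 0.023 to 0.030 without, 0.050 to 0.055 with. The plain ANOVA is conservative here.
- With no drift the two models agree (0.55 and 0.55 in one run).
- For a larger low-to-high difference of 1.4 SD and the same drift (1 SD from first to third session), power is 0.85 without period and 0.92 with it.

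**The same drift, T0-to-T1 change.** If T0 and T1 of a session share the drift d, then (T1 + d) − (T0 + d) = T1 − T0. Simulated power for the programme effect on change is about 0.55 with or without period. A period main effect added to a complete T0/T1 model with participant-by-session random effects leaves the programme-by-time estimates and their standard error (0.398) unchanged. Period can affect this contrast only through period×time, or as period in a model of the change.

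**Bias.** Over randomised orders the mean error of the programme contrast was about 0 in every scenario. Orders drawn freely from six make the estimate more variable: at 1.5 SD total drift, its SD is 0.45 without period and 0.38 with it.

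**Complete cases.** Expected completers = 15 × (1 − m)^k, where m is the assumed missing rate per unit and k the number of units that must all be present. Power is at dz 0.98.

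| Analysis | k | m = 5%: n, power | m = 10%: n, power |
|---|---|---|---|
| T0–T1, by session | 3 | 12.9, 0.90 | 10.9, 0.83 |
| With T2 as a separate attendance | 6 | 11.0, 0.83 | 8.0, 0.66 |
| With T2, each of nine samples at risk | 9 | 9.5, 0.74 | 5.8, 0.46 |

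The first two rows take power at the rounded n; the last averages over the binomial number of completers.

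**The case against.** The best defence is that the main outcome is a variation from before to after a session. Drift common to both samples cancels in it, so the period term is idle for MMP-3 and GPx. That stands, unless the within-session response itself changes over the three sessions.

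Four stronger readings are tempting, and the document supports none of them.
- **That the plan biases the programme comparison.** Order is randomised, so average bias is zero. One realised unequal list could shift the contrast by chance, but the balance of the orders cannot be judged without Figure 1, and 15 divides evenly over three orders.
- **That the plan states it will drop incomplete participants.** It does not. Complete-case use is inferred from how the named procedure works in SPSS, and missing-data rules are often left to the analysis plan. Only the choice of procedure is at issue.
- **That the intervention main effect, which averages in T0, is the chosen test.** The section compares both interventions and times, and a two-way repeated measures ANOVA gives the interaction by default.
- **That omitting a sequence term is a fault.** Sequence is a between-person term and does not change the within-person contrast when data are complete.

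**Conclusion.** The point holds in limited form. The article commits to a method that does not use the crossover structure it describes. For outcomes compared as one value per session, the loss is about 12 points of power (0.55 to 0.43) under the assumed drift of 0.5 SD per period and nil without drift. Whether pain, edema and flexibility fall here depends on whether they are compared as session values or as changes, which the text does not say. For the T0-to-T1 change in MMP-3 and GPx, drift shared by both samples costs nothing.

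The complete-case loss applies to every outcome. For a T0–T1 analysis it takes power from 0.94 to about 0.90 or 0.83 at 5% or 10% of sessions missing, and further if T2 is included. Drift size and missing rates are assumptions; the document gives neither. The matter is one of efficiency and is nearly free to correct.

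**What to change.** - **MMP-3 and GPx.** Replace the repeated measures ANOVA with a linear mixed model of the within-session change (or of the post value adjusted for T0), with programme and period fixed and participant random. An equivalent form on the individual values has programme, time, programme×time, period and period×time, with participant and participant-by-session random. Use all available sessions, and name the programme contrast in T0-to-T1 change as the primary test.
- **Pain, edema and flexibility.** Include period in the models.
- **Sequence.** A sequence term is optional.
- **Orders.** If not already done, block the list so that each programme occurs five times in each period. Three copies of one 3×3 Latin square (9 people) plus two of its mirror (6 people) give 15, with 3 + 2 = 5 per programme and period.

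Cost: analysis wording, a blocked list and a few degrees of freedom (28 to 26 for period in a complete one-value-per-session model). No new data are needed, and the article gives the study status as not yet recruiting.
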